#### Randomization

After baseline assessment has been completed by the adolescent, randomization will be carried out. Randomization of participants will be performed via Castor EDC (Castor Electronic Data Capture (2021.2)) by a researcher who is blind to block size and order. Randomization will take place at an individual level, stratified by primary diagnosis (depressive or anxiety disorder) and treatment site using a computer-generated block randomization schedule. To ensure that an equal number of patients are allocated to CBT and CBT + E-TRAIN, the allocation ratio will be 1:1. To prevent selection bias, all researchers will be blind to random block order. No researchers will have access to the randomization schedule. Due to the nature of the add-on design, blinding of adolescents, parents, therapists, and researchers to treatment condition is not applicable. The research assistants assessing the diagnostic interview at T2 will be blinded to treatment condition.

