### Data analyses

#### Primary outcome measures

Linear mixed models will be used to determine the effectiveness of adding E-TRAIN to CBT in reducing depressive and anxiety symptoms (measured with the RCADS25). A two-level structure will be used (Level 1: repeated measures, Level 2: patients). The overall treatment effect will first be evaluated in a model with condition and the baseline value of the outcome. Second, between-group differences at each time-point will be examined by adding time and the interaction of time and condition to the model. Time will be treated as a categorical variable, represented by dummy variables. Furthermore, as a sensitivity analysis, we will fit a model adjusted for the total number of completed CBT sessions and other potentially relevant confounders. Imputation of missing data will not be necessary because we will use mixed-model analyses, which adequately handles missing values [98]. Analyses will be conducted on the entire randomized sample (i.e. intention to treat) and on the per protocol/treatment completers sample. For the treatment completers sample of the experimental (E-TRAIN) condition, adolescents who completed ≥ 66% of the online sessions (four sessions or more) will be regarded as completers. The aforementioned main analyses will also be conducted separately for those with a primary diagnosis of depressive disorder, and for those with a primary diagnosis of anxiety disorder. Analyses will be conducted using SPSS version 26 + and R version 3.0 + . Statistical significance will be set at α < 0.05.

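### Randomisation is stratified by primary diagnosis and site, but neither step of the primary model includes these factors, so any prognostic value they add beyond baseline is lost to a mildly conservative test

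*Protocol article*

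**What the plan says.** **Randomisation section.** Allocation is individual and "stratified by primary diagnosis (depressive or anxiety disorder) and treatment site using a computer-generated block randomization schedule"; "the allocation ratio will be 1:1".

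**Data analyses, Primary outcome measures.** The model is set out term by term:
- Step 1: the overall effect is assessed "in a model with condition and the baseline value of the outcome".
- Step 2: "between-group differences at each time-point will be examined by adding time and the interaction of time and condition to the model". The contrast at T2, the primary time point, comes from this step.
- Levels: "A two-level structure will be used (Level 1: repeated measures, Level 2: patients"). There is no site level.
- Sensitivity model: "adjusted for the total number of completed CBT sessions and other potentially relevant confounders". The stratification factors are not named.
- Separate analyses: the main analyses "will also be conducted separately for those with a primary diagnosis of depressive disorder", and likewise for primary anxiety disorder.

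**Data analyses, Secondary outcome measures.** The same procedures are carried over. Linear mixed models are used for the questionnaire and rating-scale outcomes, and a generalised linear mixed model for presence of a disorder on the MINI (KID).

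**The concern.** Stratified blocks keep the arms balanced on diagnosis and site. That balance removes chance imbalance on these factors from the treatment contrast, so the contrast varies less from trial to trial. A model without the factors does not register this: whatever outcome variance they explain stays in its error term. The reported standard error then exceeds the true one, confidence intervals are wider than they need be, and the test rejects less often than its nominal level. The precision that stratification bought is not collected.

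This is not a detail left to an analysis plan. The article lists the terms of its main model, and an analyst who follows that list would leave the strata out.

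**Working it through.** **Inputs from the article.** Two stratification factors, 1:1 allocation, a model with condition and baseline (then time and time by condition), two-sided α = 0.05, target power 0.80, d = 0.40, N = 138 (69 per arm).

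**Input not in the article.** R², the share of residual variance in follow-up RCADS25, after baseline RCADS25, that diagnosis and site explain. It is assumed, over a range that includes zero.

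**The plan's own figure.** The article gives no figure for the effect of the strata. The nearest is N = 138. A plain two-group comparison needs 2 × (1.960 + 0.842)² / 0.40² = 98.1, so 99 per arm. The stated 69 per arm is reached only with an input the article does not state, for example a baseline correlation of 0.70: 99 × (1 − 0.49) = 50.5, so 51, and 51 × 1.35 = 68.85, so 69. That is a separate matter, and nothing below depends on it.

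**Closed form.** Under stratified allocation the true standard error is close to that of the adjusted model. The unadjusted model reports one larger by 1/√(1 − R²), so its effective critical value is c = 1.960/√(1 − R²). Then:
- type I error = 2 × [1 − Φ(c)]
- power, where the adjusted test has 80% = Φ(1.960 + 0.842 − c)

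| Assumed R² | SE ratio | c | Type I error | Power, unadjusted |
|---|---|---|---|---|
| 0 | 1.000 | 1.960 | 5.0% | 80% |
| 0.02 | 1.010 | 1.980 | 4.8% | 79.4% |
| 0.05 | 1.026 | 2.011 | 4.4% | 78.5% |
| 0.10 | 1.054 | 2.066 | 3.9% | 76.9% |

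The matching coverage of a nominal 95% interval is 95.0, 95.2, 95.6 and 96.1%.

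**Simulation check.** Stratified permuted blocks with two diagnoses and two sites, N = 138 all analysed, d = 0.40, one follow-up, 8,000 runs per setting. Block size 4 and baseline correlation 0.5 are assumed. Each cell gives the result without, then with, the strata in the model.

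| Assumed R² | Model SE | Type I error | Power |
|---|---|---|---|
| 0 | 0.148 / 0.148 | 0.054 / 0.053 | 0.76 / 0.76 |
| 0.02 | 0.148 / 0.146 | 0.048 / 0.050 | 0.76 / 0.77 |
| 0.05 | 0.148 / 0.144 | 0.044 / 0.051 | 0.77 / 0.79 |
| 0.10 | 0.148 / 0.140 | 0.038 / 0.048 | 0.77 / 0.81 |
| 0.20 | 0.148 / 0.132 | 0.029 / 0.049 | 0.78 / 0.85 |

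The unadjusted model's standard error stays at 0.148 throughout, while the actual spread of its estimates falls to about 0.140 at R² = 0.10 and 0.133 at R² = 0.20. Monte Carlo error is about 0.002 on type I error (√(0.05 × 0.95/8000)) and 0.005 on power. The absolute power values depend on the assumed correlation; the point is the difference within each row.

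**The case against.** **The loss is conditional.** At R² = 0 nothing is lost, and the article gives no evidence on how far diagnosis or site predicts outcome at equal baseline score. Its Background says the two disorders often occur together, which may limit what a binary primary-diagnosis label adds. This stands. A reader might infer that the standard errors will be too large; the article supports only that they will be if the factors carry residual prognostic value. Equally, nothing shows that baseline RCADS25 absorbs both factors: the total score pools 15 anxiety and 10 depression items and does not encode site.

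**The effect is small and in the safe direction.** This also stands. The power loss is 0.6, 1.5 or 3.1 points at R² of 2, 5 or 10%, and false positives do not increase.

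**Other planned analyses cover the factors.** They do so only in part. The separate analyses by diagnosis hold diagnosis fixed but still omit site, and they leave the pooled estimate unchanged. The unnamed confounders might include the strata, but only in a sensitivity model.

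**The figures do not extend to every secondary outcome.** This stands for the MINI (KID). With a logit link, adjustment changes the odds ratio being estimated and generally does not shrink its standard error. A reader might carry the table over to that outcome, but the linear argument does not support it.

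**The sample size is a separate question.** A reader might treat this as more serious because the power claim is itself open to doubt. How N = 138 was derived neither strengthens nor weakens this point.

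**Conclusion.** The point holds as a conditional matter of efficiency. The randomisation and the stated model do not match: two factors fix the allocation, and neither appears in step 1 or in step 2, which yields the T2 contrast. The consequence is a mildly conservative analysis, without bias and without inflated type I error. Over assumed residual R² values from 0 to 10%, type I error runs from 5.0% down to 3.9%, and power from 80% down to 76.9% for a test that would have 80% when adjusted.

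These figures rest on the assumed R², on a linear model, and on blocks that keep the strata close to balanced. The omission itself is certain from the text; the size of the loss is not known. The change is worth making because it costs almost nothing.

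**What to change.** - **Primary model.** Add primary diagnosis (depressive or anxiety) and treatment site as fixed covariates in both step 1 and step 2.
- **Continuous secondary outcomes.** Make the same addition to their linear mixed models.
- **Added sites.** The recruitment section allows further sites, so state before unblinding how very small ones will be pooled.
- **MINI (KID).** Adjust for the stratification factors here too. State that, with a logit link, the adjusted odds ratio is a conditional estimand, and do not claim the precision gain computed for the linear models. The interview is planned at six months only, so there is no baseline value of this outcome to adjust for.
- **Analyses within each diagnosis.** Keep site in the model; diagnosis is constant there.

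The cost is a short change of wording and a few degrees of freedom. No new data are needed and N does not change. The change should be fixed before unblinding so that the choice of covariates cannot depend on results.

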#### E-TRAIN therapists

Patients will be guided by a psychologist who has been trained in the application of E-TRAIN. After each online session, these E-TRAIN therapists will provide feedback and guidance using secured messages within the online platform. To ensure treatment integrity, E-TRAIN therapists will receive a detailed treatment protocol with standardized feedback templates. E-TRAIN will take place simultaneously to CBT, and will start after the first 2–4 CBT sessions. Based on the patient’s preference, the six sessions of E-TRAIN will be completed on either a weekly or fortnightly schedule; hence, E-TRAIN will be completed in 6 to 12 weeks. All adolescents will be guided by an E-TRAIN therapist other than their CBT therapist.

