##### Therapist measures

The CBT therapist of each participant will be asked to report the following: number of CBT sessions, content and number of sessions of non-CBT care. Additionally, the E-TRAIN therapist will be asked to fill in an adapted version of the System Usability Scale to measure the usability of the online intervention (SUS) [97].

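### The sensitivity model adjusts for completed CBT sessions as if they were a confounder, but the count arises after randomisation, so the model cannot show whether the primary result is robust

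*Protocol article*

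**What the plan says.** In the protocol article, Data analyses, Primary outcome measures, the main model comes first: "The overall treatment effect will first be evaluated in a model with condition and the baseline value of the outcome". Time and its interaction with condition are added in a second step. The text then states that, as a sensitivity analysis, "we will fit a model adjusted for the total number of completed CBT sessions and other potentially relevant confounders". The word before the last three places completed CBT sessions among the confounders. The next section, Secondary outcome measures, carries the same procedures over to the secondary outcomes.

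Three other places fix the timing and source of the count:
- Randomization: "After baseline assessment has been completed by the adolescent, randomization will be carried out".
- E-TRAIN therapists: "E-TRAIN will take place simultaneously to CBT, and will start after the first 2–4 CBT sessions". The same section says that "E-TRAIN will be completed in 6 to 12 weeks".
- Therapist measures: the CBT therapist reports "number of CBT sessions, content and number of sessions of non-CBT care". The Randomization section says that therapists and adolescents are not blinded.

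CBT is regular care in both arms. The article's description of it sets no fixed number of sessions.

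**The concern.** A confounder in a treatment comparison is a common cause of treatment and outcome. Allocation here is random, so nothing that happens later can be a cause of it. Except possibly for the first few sessions, the total number of CBT sessions accrues while one arm is receiving E-TRAIN and the other is not. Arm, early improvement, engagement and drop-out can all plausibly influence it.

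This matters in two ways. If E-TRAIN works partly by changing how much CBT an adolescent completes, adjustment removes that part of the effect (mediation). If unmeasured severity drives both session number and symptoms, adjustment opens a path between arm and severity that randomisation had closed (collider bias). Either way the adjusted coefficient answers a different question from the main model. A sensitivity analysis is read as support for the main result or as a warning against it, and this one could give either signal for reasons unrelated to the validity of that result.

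**Working it through.** The plan gives no figure on this point to reproduce. The only planning figure used is the design effect of d = 0.40 (Sample size), as a yardstick. Every other input below is assumed.

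**Set-up.** Arm A is 0 or 1. B is the baseline outcome. U is unmeasured severity with SD 1 and correlation ρ with B. The session count in SD units is S = s·A + λ·U + noise, where s is the shift caused by E-TRAIN. The outcome in SD units depends on A, B and 0.5·U. Sessions have no effect of their own on the outcome.

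**Formula.** In a regression on A, B and S, the coefficient of S is

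β = 0.5·λ·(1 − ρ²) / (1 − λ²·ρ²),

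and the bias in the arm coefficient is −s·β. It is zero when s = 0. Its sign reverses with the sign of s or of λ.

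**Size of the bias (absolute value, SD units).**

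| ρ | s = 0.3, λ = 0.3 | s = 0.5, λ = 0.7 |
|---|---|---|
| 0 | 0.3 × 0.150 = 0.045 | 0.5 × 0.350 = 0.175 |
| 0.7 | 0.3 × 0.0765/0.9559 = 0.024 | 0.5 × 0.1785/0.7599 = 0.117 |
| 0.9 | 0.3 × 0.0285/0.9271 = 0.009 | 0.5 × 0.0665/0.6031 = 0.055 |

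Against 0.40, the row for ρ = 0 is 11% to 44%. The row for ρ = 0.7 is 6% to 29%.

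**Simulation check.** 400,000 patients, ρ = 0, λ = 0.5, true effect −0.40, no CBT-dose effect. The model with arm and baseline only returned −0.40 throughout. With the session count added:

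| Shift in sessions | Adjusted estimate |
|---|---|
| 0 | −0.40 |
| −0.3 SD | −0.33 |
| −0.5 SD | −0.28 |
| +0.3 SD | −0.48 |
| +0.5 SD | −0.53 |

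With a true effect of zero, shifts of −0.5 and +0.5 SD gave +0.12 and −0.13. The formula gives 0.5 × 0.5 × 0.5 = 0.125 in absolute value.

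**Mediation alone.** With a direct effect of −0.20, a shift of 0.5 SD and an effect of −0.40 per SD of sessions, the total effect is −0.20 − 0.5 × 0.40 = −0.40. The adjusted model returned −0.20. Both numbers are correct, but for different questions.

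**Time-points.** The text does not say whether the adjusted model is the overall-effect model or the one by time-point. If it is fitted by time-point, a single total includes sessions given after T1, so the T1 contrast would be conditioned on later events that T1 symptoms may have influenced.

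**The case against.** The best defence has four parts.

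- **It is secondary.** The text introduces the model with "Furthermore, as a sensitivity analysis, we will fit a model adjusted for", after the main model. No decision rule in the article depends on it. This stands: the primary estimate is untouched.
- **Bias is conditional.** A reader might infer that the adjusted model is certainly biased. The documents do not support that. Nowhere do they say that E-TRAIN changes the number of CBT sessions or that more severely ill adolescents receive more of them, and a therapist other than the CBT therapist delivers E-TRAIN. Without a shift, the calculation shows no bias.
- **Baseline is already in the model.** A reader might take 11% to 44% of the design effect as the expected distortion. That range requires a severity factor unrelated to the baseline outcome. Baseline symptoms probably capture part of severity, which lowers the figures, and the honest range starts at zero.
- **The question is legitimate.** In an add-on trial it is reasonable to ask whether the arms received different amounts of CBT. This also stands, but it calls for a description by arm or a direct-effect analysis. The latter needs the assumption that sessions and outcome share no unmeasured cause, which randomisation does not secure.

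A further tempting claim is that this model would manufacture an effect. Take 51 to 69 analysed per arm (69/1.35 = 51) and an assumed baseline correlation of 0.5 to 0.7. The standard error √[(2/n)(1 − r²)] is then about 0.12 to 0.17 SD. A bias of 0.045 raises the 5% false-positive rate only to about 6–7%. Only the extreme 0.175 raises it to about 18–30%.

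**Conclusion.** The point holds. The article positively names a post-randomisation variable as a confounder, so this is not a detail left to an analysis plan. The resulting model does not in general estimate the total effect that the main model targets and cannot serve as a check on it. The same applies to the secondary outcomes.

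The reach is limited. The primary estimate is unaffected, and both the existence and the direction of any bias depend on whether and how E-TRAIN changes session number. As an illustration only, the bias is zero with no shift. With a shift of 0.3 to 0.5 SD it is about 0.02 to 0.12 SD if shared severity correlates 0.7 with baseline, and at most about 0.18 SD if it is unrelated to baseline. The T1 problem arises only if the adjusted model is fitted by time-point. This should be corrected before analysis, but it is not an error in the primary analysis.

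**What to change.** 1. Remove completed CBT sessions from the sensitivity model.
2. Adjust only for covariates measured at T0 and named before data analysis, starting with the stratification factors, primary diagnosis and treatment site. A date before analysis is the right marker, because most parties are not blinded.
3. Report CBT and non-CBT sessions by arm descriptively. The CBT therapists already supply these data.
4. If the role of CBT dose is of interest, present any session-adjusted model as exploratory mediation. State its assumptions, in particular no unmeasured common cause of sessions and outcome. For a T1 contrast, count only sessions up to T1.
5. Apply the same change to the secondary outcomes.

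The cost is wording only: no new data, and no change to the primary model or the sample size. The one loss is that the question of CBT dose becomes exploratory.

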### Procedure

#### Recruitment and consent

Participants will be recruited at the youth departments of Arkin and GGZ Oost Brabant, two Dutch mental health centres. Other additional treatment sites may be added. All adolescents will be screened for eligibility during the intake by a clinician, who assesses inclusion and exclusion criteria. Diagnoses will be established by a psychiatrist or a registered Health Care Psychologist (Dutch: "Gezondheidszorg-psycholoog") on DSM-5 criteria. After the intake, eligible adolescents and their parents or caregivers will receive written study information and the informed consent forms. If the eligible adolescents agree to be approached, a research assistant will contact them by telephone and provide further information about participation in the study. If adolescents agree to participate in the study, they will be asked to sign the informed consent form. Both parents will be asked to sign the informed consent form for their child’s participation if the patient is < 16 years. Additionally, one of the parents will be asked to participate in the study and fill in questionnaires as well. This parent will also be asked to sign an informed consent form regarding their own participation.

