#### Secondary outcome measures

Linear mixed models will also be used to determine the effectiveness of the internet-based emotion regulation training with regard to 1) depressive symptoms (CDI-2); 2) anxiety symptoms (SCARED); 3) parent-report depressive and anxiety symptoms (SCARED-P and CDI-P); 4) therapist-report global functioning, symptom severity and improvement (CGAS and CGI); and 5) self-report emotion (dys)regulation (FEEL-KJ and DERS). Generalized linear mixed model analysis will be used to determine the effectiveness of the internet-based emotion regulation training on the presence of a depressive and/or anxiety disorder (MINI (KID)). The aforementioned procedures will be followed for these secondary analyses.

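### For the parent- and therapist-reported outcomes, the claim that mixed models make imputation unnecessary does not cover a missing baseline covariate, so adolescents without that informant's T0 form are dropped

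*Protocol article*

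**What the plan says.** The relevant text is in the Protocol article.

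- **Model** (Data analyses, Primary outcome measures): "The overall treatment effect will first be evaluated in a model with condition and the baseline value of the outcome". Time and the time-by-condition interaction are then added to that model, so the baseline score is a covariate throughout.
- **Missing data** (same section): "Imputation of missing data will not be necessary because we will use mixed-model analyses, which adequately handles missing values".
- **Analysis set** (same section): "Analyses will be conducted on the entire randomized sample (i.e. intention to treat"), with a treatment-completers analysis alongside.
- **Carry-over** (Data analyses, Secondary outcome measures): the listed outcomes include "parent-report depressive and anxiety symptoms (SCARED-P and CDI-P") and "therapist-report global functioning, symptom severity and improvement (CGAS and CGI"), and the section ends: "The aforementioned procedures will be followed for these secondary analyses".
- **Condition for randomisation** (Procedure, Randomization): "After baseline assessment has been completed by the adolescent, randomization will be carried out". No parent or therapist form is mentioned as a condition.
- **Parents** (Recruitment and consent): "Additionally, one of the parents will be asked to participate in the study and fill in questionnaires as well". The parent signs a separate consent, and parent participation is not among the eligibility criteria under Participants.
- **CBT therapists** (Assessments): they are asked for forms at T0, T1 and T2.

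**The concern.** A likelihood-based mixed model uses whatever outcome records a patient has, so a missing T1 or T2 score does not remove the patient. It makes no such provision for a covariate. A record with a missing covariate cannot enter the likelihood, and standard SPSS and R routines delete it. A baseline covariate takes the same value on all of a patient's records, so one missing T0 form removes every follow-up rating of that outcome.

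The reason given for not imputing is therefore wrong for this covariate, and as written it rules out the usual remedy. The parent and therapist scales are the only continuous effectiveness outcomes in the analysis plan that the unblinded adolescent does not report. Observed six-month ratings on them would be discarded because a different visit is missing, and the analysis would fall short of the declared intention-to-treat set.

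**Working it through.** The plan has no figure of its own to reproduce here. Its N = 138 belongs to the RCADS25 and is not in dispute.

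**Which outcomes are exposed**

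- RCADS25, CDI-2, SCARED and self-reported FEEL-KJ and DERS: not exposed, because the adolescent's T0 precedes randomisation.
- MINI (KID): not exposed, because it is assessed at T2 only and has no baseline score.
- CGI-Improvement: left out, because it rates change against earlier ratings.
- SCARED-P, CDI-P, CGAS and CGI-Severity: exposed. Each has a T0 form in Table 1, and none is required before allocation.

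**Inputs**

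- From the article: 138 randomised, 69 per arm, effect 0.40 SD, 35% extra inclusion for drop-out. Reading the last as a factor of 1.35, 138/1.35 = 102.2 are retained. That is 74%, so 26% are missing at T2.
- Assumed, because the article gives no value: share m of informant T0 forms missing (10%, 20%, 30%, at random) and correlation ρ = 0.5 between visits.

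**Patients removed.** 138 × m = 13.8, 27.6 and 41.4, leaving about 124, 110 and 97. This is an upper bound on the avoidable loss, because it includes adolescents whose informant also gives no follow-up rating.

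**Loss of precision, closed form.** Consider the T2 visit alone. A patient with T0 contributes information proportional to 1/(1 − ρ²). A patient without T0 contributes 1 if kept and 0 if dropped. The ratio of standard errors, planned model over a model that keeps everyone, is

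SE ratio = √[1 + m(1 − ρ²)/(1 − m)]

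With 1 − ρ² = 0.75:

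- m = 10%: √(1 + 0.75 × 0.1/0.9) = √1.083 = 1.04
- m = 20%: √(1 + 0.75 × 0.2/0.8) = √1.188 = 1.09
- m = 30%: √(1 + 0.75 × 0.3/0.7) = √1.321 = 1.15

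**Loss of precision, simulation.** The closed form ignores T1, which adds information on the patients kept. The simulation used 69 per arm, three equally correlated visits, effect −0.40 SD at T1 and T2, and 26% missing T2, half of them also missing T1. It compared the baseline-covariate model, with patients lacking T0 dropped, against T0 as a response with a common mean across arms. The SE ratios for the T2 contrast were about 1.05, 1.10 and 1.16 to 1.17.

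**Variant.** With complete T1 and T2, ρ = 0.6 and one overall treatment effect, the model standard errors were:

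| T0 missing | Planned | T0 as response | Ratio |
|---|---|---|---|
| 10% | 0.119 | 0.115 | 1.03 |
| 20% | 0.127 | 0.118 | 1.08 |
| 30% | 0.135 | 0.122 | 1.11 |

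Filling the missing baseline with the overall mean also kept all 138. With T0 missing completely at random, none of the models showed material bias.

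**The case against.** **The loss may be small.** The article gives no non-return rate. Parents receive the T0 link, an email reminder after five days and a telephone call after one week, so 20% or 30% is only an assumption. This stands: the shortfall arises only if forms are missing. No comparable reminder is described for CBT therapists.

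**This is detail for the full protocol or analysis plan.** That would be fair had the article been silent. Instead it gives a reason that is incorrect for covariates and concludes that no imputation is needed.

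**Some patients cannot be recovered.** Where an informant never responds, no model helps. This stands, and it limits the point to adolescents with a T1 or T2 rating but no T0.

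**A reader might infer that the deletion biases the comparison and that T0-as-response cures it.** The documents do not support this, because nothing in them says why forms would be missing, and the answer reverses with the mechanism. Take 20% missing in the E-TRAIN arm only, ρ = 0.5 and a true effect of −0.40:

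- If missingness follows the T0 score itself, the planned model is essentially unbiased (−0.39 to −0.41) and T0-as-response is biased (−0.34 to −0.36).
- If it follows underlying severity, the planned model is biased (about −0.46) and T0-as-response is closer (about −0.38).

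Neither model is uniformly safer.

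**The common T0 mean needs T0 to precede allocation, which is not guaranteed for these forms.** This also stands, and it has to be built into the fix.

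**Conclusion.** The point holds for SCARED-P, CDI-P, CGAS and CGI-Severity. For these outcomes the stated reason for not imputing is wrong as regards the baseline covariate. Each adolescent with a missing informant T0 loses observed follow-up, and the analysis is then not of the entire randomised sample.

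The cost is precision: about 5%, 10% and 16% on the standard error of the T2 contrast at an assumed 10%, 20% and 30% missing. This rests on ρ = 0.5, 26% missing T2 and T0 missing at random. It is smaller (3%, 8% and 11%) in the variant with complete follow-up and a single overall effect, and zero if every form is returned.

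Two stronger readings are not supported. The primary RCADS25 analysis is not compromised by this mechanism. Nor do the documents establish a bias, or a bias advantage for any alternative model. As these are secondary outcomes, the change is advisable but not critical to the trial's main conclusion.

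**What to change.** 1. Limit the sentence on imputation to missing outcome values, and add how a missing informant baseline is handled.
2. For SCARED-P, CDI-P, CGAS and CGI-Severity, keep patients with a missing T0 by one prespecified method. Either model T0 as one of the repeated responses with a common T0 mean across arms, or retain the baseline covariate and fill missing values without regard to arm, for example with the overall mean.
3. Count a T0 form as baseline only if it was completed before allocation, and treat a later one as a missing T0. The common-mean constraint depends on this.
4. Report the planned covariate model, in patients with a T0 form, as a sensitivity analysis, because the missingness mechanism is unknown.
5. Report, by arm and informant, how many T0 forms are missing and how many of those adolescents have follow-up ratings.

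The cost is a wording change and a few lines of code, with no new data or patients. The downside is slightly more analysis work, and reliance on T0 being a pre-allocation measure and on a missing-data assumption that cannot be tested. The RCADS25 analysis needs no change.
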